### Trial design

The POMPAE trial is a randomized, single centre, double-blind placebo-controlled superiority trial conducted in the Haga Hospital in The Hague, The Netherlands. The aim of the trial is to analyse the potential of ionized magnesium levels in the serum between 1.5 and 2.0 mmol/L to prevent de novo atrial fibrillation in patients following cardiac surgery. For clarity, if magnesium levels are mentioned, they always indicate ionized magnesium levels.

Based on the protocol, upon initiation of anaesthesia, a continuous infusion of study medication (magnesium sulphate or Ringer’s lactate (placebo)) is initiated based on a magnesium level determined within the 72 h prior to surgery. If the preoperative level is below 1.0 mmol/L, the study infusion is preceded by a bolus of 10 mmol of magnesium to achieve stable magnesium levels in plasma. This study protocol (see ‘Trial intervention’ section) is based on previous pharmacokinetic studies performed in similar patient groups [13, 14].

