### Randomization and treatment masking (blinding)

All patients with an indication for cardiac surgery are screened (based on Table 1) for potential participation in the POMPAE trial. For elective patients, screening is performed at the preoperative clinic visit in the cardiac surgery department. For those patients being transferred from other hospitals, screening is performed at the time of arrival in the hospital. As only semi-elective surgeries are included, patients requiring immediate surgery, i.e. type A dissections or urgent CABG, due to main stem occlusion are excluded.

After information on the trial and trial documentation (see Supplementary Table 1), patients are either approached 1–2 h later (post admission to the hospital) for informed consent or, for those with elective surgery, directly upon admission. After inclusion, randomization is performed in Castor [15] (web-based randomization and database application) by the cardiac surgery department, see later for more details.

As part of admission routine, a magnesium level is obtained from regular blood works. The first study intervention is the administration of study medication post induction of anaesthesia. The pharmacy department receives an email post randomization with treatment allocation and prepares the trial drug. The team responsible for patient care (in the operating room (OR), intensive care unit (ICU) and later, the cardiac surgery department) remains fully blinded to treatment allocation. The study drug is labelled with the patient’s information and transported to the OR prior to the beginning of surgery. Since both MgSO_4_ and the placebo (Ringer’s lactate) are clear fluids, treatment allocation remains concealed to the anaesthesiologist and ICU staff treating the patient postoperatively. Serum magnesium levels are measured according to protocol (see ‘Trial intervention’ section). The trial participants and the study team remain blinded to treatment allocation during the conduction of the trial.

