### Outcomes

The primary aim of the POMPAE trial is to investigate the effects of magnesium sulphate on the prevention of post cardiac surgery atrial fibrillation. The primary outcome is the incidence of postoperative atrial fibrillation (POAF) in the first 7 postoperative days (censored at hospital discharge) consisting of newly diagnosed AF over a period of 5 min or longer by ECG recording. The secondary study parameters/endpoints are AF during the 28 days post-surgery, the duration of POAF and peak heart rate recorded, hospital and ICU lengths of stay, the duration of mechanical ventilation and duration of inotropic or vasopressor support. Also, the combined outcome including 28-day post-surgery mortality, stroke, pulmonary embolism, delirium (requiring any form and/or duration of anti-psychotic medication) and infection requiring antibiotics will be measured.

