• Development or presence of significant hypotension (irrespective of cause) persisting for > 1 h with the requirement of norepinephrine support of > 0.2 mcg/kg/min
• Presence or development of third-degree heart block

In relation to the POMPAE study, participant stopping rules have been formulated as depicted in Table 3. If a stopping rule occurs, study medication is permanently ceased with the continuation of ECG measurements as per protocol.

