### Statistical analysis plan

All analysis will be performed based on modified intention-to-treat principles, excluding only patients that withdrew consent or were unable to receive study medication due to logistical reasons. All eligible patients consenting to participate will be screened and randomized to maximize inclusion. However, as study medication could not be prepared by the pharmacy department outside of regular working hours, patients not able to receive medication at the start of anaesthesia, despite consent, will be excluded from analysis.

All data will initially be assessed for normality. Baseline imbalance will be determined using chi-square tests for equal proportion, Student tests for normally distributed data and Wilcoxon rank sum test for non-parametric data with results presented and *n* (%), mean (standard deviation) or median (interquartile range) respectively.

The primary outcome (POAF) and other binomial secondary outcomes will be analysed using generalized modelling (accounting for stratification variables of surgery type) with relative risk (95% CI) determined using a log binomial model. A risk difference (95% CI) determined using a binomial distribution with an identify link and odds ratios (95% CI) using a logistic binomial model will also be employed, where appropriate. Moreover, it is prescribed that sensitivity analysis will be performed adjusting for baseline imbalance (*p* < 0.2) and baseline covariates previously identified as being known to be linked to outcome (age, left ventricular function, type and length of surgery including time on CPB, use of vasopressors and inotropes). Where there is missing data for the primary outcome, multiple imputation will be employed.

To account for the competing risk of death, duration outcomes (time to POAF, lengths of stay, ventilation, inotropic or vasopressor support) will be analysed using competing risk regression with results reported as hazard ratios (95% CI) and presented as cumulative incidence curves. All analysis will be performed using SAS version 9.4 (SAS Institute Inc., Cary, NC, USA) and a two-sided *p* value of 0.05 will be used to indicate statistical significance. For the analysis of the secondary endpoints, adjustment for multiplicity will be performed using the Holm-Bonferroni method to reduce changes of type 1 error.

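### The adjusted sensitivity analysis treats length of surgery, bypass time and vasopressor or inotrope use as baseline covariates, although as collected they arise after study drug starts

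*Protocol article*

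**What the plan says.** The Statistical analysis plan section of the Protocol article specifies a primary model for POAF that accounts only for the surgery-type stratum. It then adds a further analysis: "sensitivity analysis will be performed adjusting for baseline imbalance" (at p < 0.2), and also for "baseline covariates previously identified as being known to be linked to outcome". The latter are listed as "age, left ventricular function, type and length of surgery including time on CPB, use of vasopressors and inotropes". Imbalance is judged by significance tests between the arms: "Baseline imbalance will be determined using chi-square tests for equal proportion", with corresponding tests for continuous data.

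On timing, the Trial design section says that "upon initiation of anaesthesia, a continuous infusion of study medication" is begun. The section on randomisation and blinding says: "The first study intervention is the administration of study medication post induction of anaesthesia".

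The Outcomes section names as secondary endpoints, among others, "the duration of mechanical ventilation and duration of inotropic or vasopressor support".

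**The concern.** A covariate is safe to adjust for in a randomised comparison if treatment cannot have influenced it, which in practice means that it is fixed before treatment starts. Three of the listed items do not meet that condition as the trial collects them. Vasopressor and inotrope use matters most, because the plan also analyses the duration of that support as an outcome by arm. One construct thus serves as an outcome in one place and as a baseline adjuster in another.

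If magnesium changes the use of such support, two things happen on adjustment. Any part of the effect on POAF that runs through the support is removed. And where unmeasured severity drives both support and POAF, comparing arms within levels of support compares patients of different severity. A sensitivity analysis is read as a check on robustness. One that can move for these reasons may appear to confirm or undermine the primary result when it does neither.

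The p < 0.2 rule is a smaller matter. Differences in baseline variables between randomised arms arise by chance, so the rule lets chance choose the covariates.

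**Working it through.** **1. Timing of each listed covariate**

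| Covariate | Where the Protocol article records it | Known before study drug starts? |
|---|---|---|
| Age | Eligibility criterion (Table 1); not named in Table 2 | Yes |
| Left ventricular function | Table 2, baseline row (preoperative echo) | Yes |
| Type of surgery | Table 2, screening row; stratification factor | Yes, as planned |
| Length of surgery | Table 2, perioperative row (start and end times) | No |
| Time on bypass | Table 2, perioperative row | No |
| Vasopressors and inotropes | Table 2, circulatory support in the perioperative, intensive care and ward rows | No, as collected |

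The article gives no time window for vasopressor or inotrope use, so support begun after POAF could be counted. *Use of inotropes* is also not sharply defined, since the Trial intervention section describes a milrinone bolus for all patients as routine practice before coming off bypass.

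**2. The plan's own figures**

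The plan gives no figure for this analysis. Its event rates (25% and 15%, relative risk 0.60) come from Sample size and power, where the stated size reproduces:

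n per arm = [1.96·√(2·0.20·0.80) + 0.8416·√(0.25·0.75 + 0.15·0.85)]² / 0.10² = (1.109 + 0.472)² / 0.01 ≈ 250, so 500 in total, with power 80.0%. The present point leaves this unchanged.

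**3. Illustration of the shift**

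The documents give no rate of vasopressor use and no effect of magnesium on it, so every input here except the event rates and the 1:1 allocation is an assumption. Each scenario has 1,000,000 simulated patients:

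- Treatment T is allocated 1:1; unmeasured severity U is standard normal.
- Support V: logit P(V) = −0.4 + d·T + g·U.
- POAF Y: log P(Y) = c + b·T + m·V + h·U, with c set so that control risk is 25% and risks capped at 0.95.
- The crude relative risk is compared with the Mantel-Haenszel relative risk stratified by V, which is Σ(a·n₀/n) / Σ(b·n₁/n), where a and b are the treated and control events in each stratum.

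Severity drives both V and Y, and V has no effect of its own on Y (g = 1, h = 0.4, m = 0):

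| d | Use of support, control → magnesium | True RR 1.00: crude / adjusted | True RR 0.60: crude / adjusted |
|---|---|---|---|
| 0 | 42% → 42% | 0.999 / 0.999 | 0.599 / 0.600 |
| 0.4 | 42% → 50% | 0.996 / 0.969 | 0.600 / 0.584 |
| 0.8 | 42% → 58% | 1.004 / 0.952 | 0.598 / 0.567 |
| 1.2 | 42% → 66% | 1.001 / 0.926 | 0.600 / 0.554 |

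Support acts only as a mediator (g = h = 0, m = 0.4, direct RR 0.60): total relative risks of 0.625, 0.650 and 0.673 are all adjusted to about 0.60.

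Both mechanisms together, with no direct effect: total relative risks of 1.036, 1.067 and 1.092 become 0.977, 0.950 and 0.926.

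**4. The shift against sampling error**

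With 250 per arm and 25% risk in each, SE(log RR) = √(2 × 0.75 / (250 × 0.25)) = √0.024 = 0.155. The shifts in the null column are ln 0.969 = −0.031 to ln 0.926 = −0.077, or about 0.2 to 0.5 standard errors.

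**5. The p < 0.2 rule**

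The baseline row of Table 2 names 18 items. Treated as independent, 18 × 0.2 = 3.6 are selected by chance on average, and the probability of at least one is 1 − 0.8¹⁸ = 0.98. These are counts of selected covariates, not measures of bias.

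**The case against.** The strongest reply is that this is a sensitivity analysis. The primary model adjusts only for the surgery stratum, and Table 4 also plans unadjusted intention-to-treat analyses. That is right, and it limits the weight of the point.

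A second reply is that the timing of vasopressor and inotrope use is not stated, that the Data collection section mentions baseline medication use, and that the endpoint is the duration of support while the covariate is its use. This stands in part: preoperative use is conceivable. But the baseline row of Table 2 has no entry for circulatory support, while three later rows do. For surgery length and bypass time no such reading is available.

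A third reply is that the calculation rests on inputs that the documents do not supply, and that the shift disappears if magnesium leaves vasopressor use alone. That also stands; the figures show direction and rough order only.

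Some stronger readings are tempting but not supported:

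- A reader might infer from the stopping rule on hypotension "with the requirement of norepinephrine support of > 0.2 mcg/kg/min" that the plan expects the drug to affect vasopressor need. The rule applies whatever the cause of the hypotension, so it attributes nothing to magnesium.
- A reader might infer that harm acting through hypotension would be hidden. The primary analysis would still show the total effect, and duration of support is analysed separately.
- A reader might treat surgery length and bypass time as equally damaging. The team is blinded, although the article concedes that staff may suspect allocation, so magnesium is unlikely to change them much. The illustration does not cover them.
- A reader might infer that the p < 0.2 rule biases the estimate. The material shows only that it makes the covariate set depend on the data.

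**Conclusion.** The point holds, at the level of something that should be fixed and not as a threat to the primary result. The article calls surgery length, bypass time and vasopressor or inotrope use baseline covariates, and by its own schedule of drug start and data collection they are not.

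The consequence is conditional. If magnesium alters vasopressor or inotrope use, the adjusted estimate is no longer an estimate of the randomised comparison. Under the assumed inputs a null effect is displaced to 0.97–0.93 and a true 0.60 to 0.58–0.55, in both cases towards benefit. The mediator-only scenario likewise moves the estimate below the total effect. If the drug has no effect on use, crude and adjusted estimates agree, but the plan cannot know that in advance. The p < 0.2 rule is a minor point about prespecification.

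**What to change.** In the Statistical analysis plan section:

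- Restrict the adjusted sensitivity analysis to a fixed list of covariates known before study drug starts: age, left ventricular function and planned surgery type, with EuroScore II as an option.
- Remove length of surgery, bypass time and vasopressor or inotrope use from that model, and report them descriptively or as outcomes.
- As a minor change, let the fixed list replace the p < 0.2 imbalance rule, so that baseline tests have no part in choosing covariates.

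The planned log-binomial, identity-link and logistic models can stay, because the timing defect does not require another estimator. The sample size stays at 500, with 530 recruited.

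The cost is a change of wording. The retained covariates are preoperative data; because Table 2 does not name age, the sponsor should confirm that the database captures it. The change is most credible if dated before the trial team sees results by arm. The Trial status section says that recruitment is paused for the interim analysis, so it should be made promptly.

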**Methods:**

The (POMPAE) trial is a phase 2, single-center, double-blinded randomized superiority clinical study. It aims to assess the impact of perioperative continuous intravenous magnesium administration on the occurrence of cardiac surgery-related POAF. A total of 530 patients will be included. Eligible patients will be randomized in 1:1 ratio to the intervention or placebo group with stratification based on the presence of valvular surgery. The objective of the infusion is to maintain ionized magnesium levels between 1.5 and 2.0 mmol/L.

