### Presentation of outcome data

Our proposed tables and figures for the primary manuscript describing the outcomes of the POMPAE trial are listed in Table 4.

**Table 4 Tab4:** Planned tables and figures

Proposed table and figures for the main manuscript
• Table 1: Baseline characteristics
• Table 2: Primary and secondary outcomes
• Fig. 1: Consort diagram showing assessment of patient eligibility, random assignment of patients, analysis population and flow of patients in the POMPAE trial
• Fig. 2: Ionized magnesium levels in treatment and placebo group
• Table 3: Compliance to POMPAE medication delivery protocol
Proposed table and figures for the supplementary appendix of the main manuscript
• Table S1: Additional baseline characteristics
• Table S2: Protocol deviations and intervention altered compared to protocol
• Table S3: Rescue therapies employed during trial
• Table S4: (Serious) adverse events and stopping rules applied
• Table S5: Analysis of primary and secondary outcomes between stratification groups
• Table S6: Unadjusted analyses in the intention-to-treat population
• Figure S1: Mean, lowest and highest Mg level during intervention period by treatment group
• Figure S2: Time-weighted mean ionized Mg level during intervention period by treatment group

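### The binary-outcome models account for the randomisation stratum (valvular surgery), but no such term is stated for the competing risk regressions of the duration outcomes; if it is left out and is prognostic, those secondary tests lose some power

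*Protocol article*

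**What the plan says.** The Abstract (Methods) of the protocol article has patients "randomized in 1:1 ratio to the intervention or placebo group with stratification based on the presence of valvular surgery".

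The section *Statistical analysis plan* then assigns models by type of outcome.

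- **Binary outcomes.** POAF and "other binomial secondary outcomes will be analysed using generalized modelling (accounting for stratification variables of surgery type"), with a log binomial model for the relative risk.
- **Duration outcomes.** The next paragraph takes the "duration outcomes (time to POAF, lengths of stay, ventilation, inotropic or vasopressor support") and says that they "will be analysed using competing risk regression with results reported as hazard ratios (95% CI) and presented as cumulative incidence curves". It gives the reason (death as a competing risk), the effect measure and the display. It lists no model terms and does not mention the stratum.

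Three other places bear on the question. A sensitivity analysis, described in the binary-outcome paragraph, adjusts for covariates that include "type and length of surgery including time on CPB, use of vasopressors and inotropes". The list of planned tables contains "Table S5: Analysis of primary and secondary outcomes between stratification groups" and "Table S6: Unadjusted analyses in the intention-to-treat population".

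**The concern.** The plan states adjustment for the stratum for one class of outcome and is silent for the other. An analyst who follows the text literally would fit the duration models with treatment alone.

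Leaving a prognostic stratification factor out of a hazard model has two effects. First, the hazard ratio is non-collapsible: the ratio without the factor is a marginal quantity that lies nearer 1 than the within-stratum ratio. Second, stratified randomisation has balanced the factor between arms, but the model's standard error takes no credit for that balance. The test then runs below its nominal level and power is lost.

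Four of the eight secondary endpoints in *Outcomes* are analysed this way (hospital stay, ICU stay, ventilation, inotropic or vasopressor support), as is time to POAF. The secondary endpoints are also tested under Holm-Bonferroni, so they have little power to spare.

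**Working it through.** **1. The plan's own figure.** *Sample size and power* gives 500 patients for 25% vs 15%, 80% power, two-sided 0.05. With pooled variance and no continuity correction, n per arm = [1.96·√(2·0.20·0.80) + 0.8416·√(0.25·0.75 + 0.15·0.85)]² / 0.10² = (1.109 + 0.472)² / 0.01 = 250, so 500 in total. The figure reproduces. It concerns the binary primary outcome, which this point does not touch.

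**2. Model.** Let the hazard be h₀(t)·θ^x·γ^s, with x = treatment and s = valvular surgery. If only x is fitted, the patients still at risk at later times come increasingly from the slower stratum, and more so in the arm that reaches the event faster. The treatment ratio averaged over strata therefore drifts towards 1. The drift is small when few patients reach the event and larger when nearly all do.

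**3. Inputs.**
- From the document: N = 500, 1:1 allocation balanced within stratum, 25% vs 15% POAF.
- For time to POAF: θ = ln(0.85)/ln(0.75) = 0.565.
- Assumed for the durations, because the document sets no target for them: θ = 1.285 for reaching discharge or extubation. With 500 events this gives power Φ(√500/2 · ln 1.285 − 1.96) = Φ(0.84), about 80%.
- Assumed: the stratum hazard ratio γ (varied, as the document gives none), two equal strata and no deaths.

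**4. Simulation**, 6000 runs per row, hazard regression without and with stratification by valvular surgery. Monte Carlo standard error is √(0.79·0.21/6000), about 0.5 points, for power and √(0.05·0.95/6000), about 0.3 points, for type I error.

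| Outcome | γ | HR without / with | Power without / with (%) | Loss (points) | Type I error without / with (%) |
|---|---|---|---|---|---|
| Time to POAF | 1.5 | 0.565 / 0.563 | 80.8 / 80.8 | 0.0 | 5.1 / 5.3 |
| Time to POAF | 2 | 0.567 / 0.563 | 79.7 / 80.4 | 0.7 | 4.7 / 5.1 |
| Time to POAF | 3 | 0.571 / 0.562 | 78.6 / 80.2 | 1.6 | 4.2 / 4.9 |
| Stay, ventilation | 0.80 | 1.282 / 1.286 | 78.0 / 78.3 | 0.3 | 4.8 / 5.0 |
| Stay, ventilation | 0.67 | 1.276 / 1.287 | 77.7 / 79.3 | 1.6 | 4.3 / 4.9 |
| Stay, ventilation | 0.50 | 1.258 / 1.286 | 73.2 / 79.2 | 6.0 | 4.1 / 5.3 |
| Stay, ventilation | 0.33 | 1.231 / 1.286 | 65.1 / 79.1 | 14.0 | 3.2 / 5.1 |

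**5. Robustness.**
- With 2% deaths kept in the risk set (3000 runs), duration power was lower throughout, but the loss was much the same: 58.5% vs 65.0% at γ = 0.50 and 51.0% vs 65.4% at γ = 0.33.
- A separate simulation with 40% valvular surgery gave 78.5% vs 80.0% at γ = 0.7, 76.1% vs 79.9% at 0.6 and 73.8% vs 80.1% at 0.5.
- In that simulation, at Holm's first step for eight endpoints (0.05/8 = 0.00625), power was 46% vs 52% at γ = 0.6 and 42% vs 52% at γ = 0.5.

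**The case against.** The strongest objection is that omission is inferred from silence. A reader might infer that the plan excludes the stratum from the duration models. It does not say so: the sentence names a model family and lists no terms at all. The article condenses a fuller protocol, the SAP is not shown, and the terms of a secondary model may be stated there. Placing unadjusted analyses in a supplementary table also suggests that the main analyses are adjusted. This stands, and the point must be put conditionally. What remains is that the article does not leave adjustment wholly to another document. It states it for the binary outcomes and not for the durations. Table S6 does not say which outcomes or covariates it means, and the sensitivity analysis that includes type of surgery sits in the binary-outcome paragraph.

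A second objection is that the loss depends on a prognostic effect that the documents do not give. This stands too. If valvular surgery does not affect the durations, nothing is lost. The plan does list type of surgery among covariates known to be linked to outcome, but gives no size.

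Third, the marginal hazard ratio is a different estimand and not a biased estimate of the conditional one. This is correct, so it would be wrong to call the reported hazard ratios simply biased. The conservative test and the loss of power do not depend on that choice of words.

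Finally, the simulations set the treatment effect so that power is near 80%, ignore deaths or treat them simply, and the 0.00625 level applies only to the smallest p-value. These limits affect the exact figures but not the direction.

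**Conclusion.** The point holds in a limited form. The stratum is stated for the binary-outcome models and not for the competing risk regressions. If the latter are fitted with treatment only, and if valvular surgery is prognostic, the hazard ratios for the four duration endpoints move towards 1 and their tests become conservative. Under the assumptions above, the cost is about 0 to 2 points of power at a stratum hazard ratio of 0.67 to 0.80, about 6 points at 0.5 and about 14 points at 0.33.

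Two stronger readings are not supported. Time to POAF is hardly affected (about 0 to 2 points up to a stratum hazard ratio of 3), so the argument should not rest on it. Nor is the trial's main conclusion at risk: the primary model already accounts for the stratum, and any error in the duration tests is conservative. This is a minor improvement to secondary analyses.

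**What to change.** In *Statistical analysis plan*, add to the sentence on duration outcomes: *All competing risk regressions will account for the randomisation stratum (valvular surgery yes/no), as a covariate or as stratified baseline hazards, as in the models for the binary outcomes.* Choose one of the two forms before the final unblinding, so that no later choice between adjusted and unadjusted hazard ratios arises. If the full protocol or SAP already says this, the article needs only to agree with it.

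The cost is one sentence and one model term. Surgery type is already recorded and used for randomisation, so no data or patients are added. The only downside is that the hazard ratio becomes conditional on stratum, as the adjusted binary-outcome models already are.
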